# SYNOPSIS

| **Name of Investigational Product:** Ruxolitinib | |
| --- | --- |
| **Title of Study:** Ruxolitinib-Corticosteroid as First-Line Therapy for Newly Diagnosed High-risk Acute Graft Versus Host Disease: A Multicenter, Randomized, Phase II Controlled Trial | |
| **Protocol Number:** S2019-177 | **Study Phase:** 2 |
| **Indication:** Acute graft-versus-host disease | |
| \| **Primary Objective** \| **Primary Endpoint** \| \| --- \| --- \| \| Compare the efficacy of ruxolitinib in combination with corticosteroids versus corticosteroids in terms of overall response rate (ORR) at Day 28 in subjects with acute graft-versus-host disease (acute GVHD). \| ORR at Day28, defined as the proportion of participants demonstrating a complete response (CR), or partial response (PR) \| \| **Secondary Objective** \| **Secondary Endpoints** \| \| Compare additional response and longer-term efficacy outcomes between treatment cohorts. \| Durable ORR at Day56, defined as the proportion of patients in each arm whose response on day 28 lasts until day 56 after randomization. \| \| DOR at Month 6 for responders will be calculated. The DOR is defined from the time of the onset of response to loss of response. Subjects who died or discontinued will be censored at the  death date or the previous assessment. \| \| Response duration, defined as the time from the first response to the first recurrence/progression of acute GVHD or additional immunosuppressants for GVHD. \| \| NRM at Month 24, defined as the time from enrollment to death due to any causes other than hematologic disease relapse. \| \| Cumulative incidence of relapse (CIR) at Month 24, defined as the proportion of subjects whose underlying hematologic disease relapses. \| \| Disease-free survival (DFS) at Month 24, defined as the time from enrollment to relapse of primary disease or death from any causes, whichever occurred first. \| \| Failure-free survival (FFS) at Month 24, defined as the time from randomization to disease relapse or progression, non-relapse mortality, or the addition of new therapy for acute GVHD. \| \| Overall survival (OS) at Month 24, defined as the time from randomization to death due to any causes. \| \| Assess the incidence and severity of adverse events (AEs) and serious adverse events. \| Clinical safety data (eg, AEs, infections) will be tabulated and listed. \| \| Evaluate the use and discontinuation of  corticosteroids. \| Average and cumulative corticosteroid dose at Days 365; \| \| Evaluate the use and discontinuation of  immunosuppressive medications. \| Proportion of subjects who discontinue immunosuppressive medications at Days365. \| \| Evaluate the incidence of recurrent acute GVHD \| Incidence rate of recurrent acute GVHD through Month 24. \| \| Evaluate the incidence of cGVHD. \| Incidence rate of cGVHD at Month 24. \| \| **Overall Study Design:**  This trial is an open-label, multicenter, prospective randomized two-arm phase II study comparing the efficacy and safety of ruxolitinib plus methylprednisolone (1 mg/kg) vs. methylprednisolone (2 mg/kg) alone. The biomarkers of acute GVHD, such as sST2, sTNFR1, IL-6, IL-8, and REG3α will be tested at acute GVHD onset. Patients with newly diagnosed intermediate-risk or high-risk acute GVHD, as defined by Minnesota acute GVHD risk score and the biomarker score will be included. The treatment efficacy will be evaluated with respect to the level of biomarkers and clinical manifestations. Written informed consent must be obtained from the patients before enrollment in the study. The consent form and related materials are available from the corresponding author on request.  **Study Population:**  Eligible patients with intermediate-risk or high-risk acute GVHD graded according to the modified Glucksberg criteria, Minnesota acute GVHD risk score and the biomarker score and untreated with systemic acute GVHD therapy will be enrolled in this study.  **Key Inclusion Criteria:**   - Male or female, 14 to 65 years old. - Have undergone first allogeneic hematopoietic stem cell transplantation (allo-HSCT) from any donor source using bone marrow, peripheral blood stem cells, or cord blood for hematologic malignancies. - Develop a de novo acute GVHD, defined as intermediate- or high-risk using the Minnesota acute GVHD risk score and MAGIC biomarker algorithm.   **Key Exclusion Criteria:**   - Has received more than one allogeneic stem cell transplant. - Female patients with pregnant or breast-feeding. - Has Acquired Immune Deficiency Syndrome (AIDS), or hepatitis B/C infection, uncontrolled bacterial, fungal, or viral infections. - Allergies to ruxolitinib. - Vital organ dysfunction unrelated to GVHD, including persistent bilirubin abnormalities or severe heart and respiratory diseases. - Relapse of the primary disease or graft rejection after transplantation. - Presence of GVHD overlap syndrome. - Presence of cGVHD or associated clinical signs or DLI-induced acute GVHD or interferon. - Previous history of JAK1/2 inhibitor treatment after transplantation, except JAK inhibitors administered before the transplantation. - absolute neutrophil count (ANC) <0.5×10^9^/L or platelet count (PLT) < 20×10^9^/L - Serum creatinine > 2.0 mg/dL or creatinine clearance < 40 mL/min measured or calculated by Cockroft-Gault equation. - Patients with poor compliance should not be included in the study based on the judgment of the research team, for example if they refused to take medicine at will many times during the previous treatment.   **Study Drug, Dosage, and Mode of Administration:**  **Ruxolitinib plus corticosteroids treatment (ruxolitinib group):**  The initial dose of methylprednisolone is 1 mg/kg/day intravenously given in this arm for at least 7 days. The dosage of ruxolitinib is 5 mg PO QD. CSA will be administered intravenously at a dose of 2 mg/kg twice daily, targeting minimum concentration levels of 150–250 ng/mL. If GVHD response to treatment is assessed as PR/CR at 7 days, methylprednisolone will be tapered, followed by reduction and discontinuation of CSA and then ruxolitinib. The reduction of the methylprednisolone in the ruxolitinib group is gradual, suggesting it be tapered off over 6 weeks as follows: dosage reduced to 0.6 mg/kg/day, 0.4 mg/kg/day, 0.3 mg/kg/day, 0.25 mg/kg/day, and 0.18 mg/kg every 5 days, followed by 0.1 mg/kg/day at week 4, 0.1 mg/kg every other day after 5 days and stopped at week 6. After steroid discontinuation and CR or stable PR maintained for 6 weeks, CSA is tapered over 60 days. After CSA discontinuation and no presence of recurrent GVHD, ruxolitinib is tapered off over 90 days, which is totally maintained for approximately 6 months.  **Corticosteroid treatment (corticosteroids group):**  The initial dose of methylprednisolone is 2 mg/kg/day given twice daily for at least 7 days and then reduced. The dosage of methylprednisolone in the corticosteroids group is decreased gradually after CR and tapered off over 10 weeks as the following: dosage reduced to 1 mg/kg/day to 0.6 mg/kg/day, 0.4 mg/kg/day, 0.3 mg/kg/day, 0.25 mg/kg/day, and 0.18 mg/kg every 7 days, and then 0.1 mg/kg/day at week 4, 0.1 mg/kg every other day after 5 days, and stopped at week 10. CsA was administered intravenously at a dose of 2 mg/kg twice daily, targeting minimum concentration levels of 150–250 ng/mL. The recommended duration of CsA is 6 months.  In both arms, for refractory acute GVHD, i.e., the progression of GVHD after 3 days of therapy, no improvement within 7 days, or no CR after 14 days of therapy, the second-line therapy will be started. For refractory acute GVHD or recurrent acute GVHD, basiliximab may be used as second-line therapy, and other alternative drugs included methotrexate or mesenchymal stem cells may be used at the researcher’s decision. For refractory acute GVHD, methylprednisolone is discontinued and CsA is continued in both arms. Prolonged maintenance of ruxolitinib is used in the ruxolitinib group. A standardized follow-up booklet is given to each enrolled patient for recording the dose, frequency, and administration method of the drugs. **Estimated Duration of Participation:** Subject participation is expected to average 24 months, which includes the following:   - A screening period lasting up to 28 days. - A treatment period lasting as long as the subject is benefiting from treatment. - A safety follow-up period lasting 180 days after treatment ends. - A survival follow-up period lasting until death or study withdrawal. \| \| \| **Estimated Number of Subjects:** 198 subjects. \| \| \| **Principal Coordinating Investigator:** [name] \| \| \| **Statistical Methods:**  The sample size is calculated according to the primary endpoint (ORR) of the study. Based on our published phase I study of 32 acute GVHD patients who received steroids as first-line therapy, an expected proportion of 55% for the patients treated with corticosteroids only was established. Based on our published data of patients with acute GVHD grade I–IV who received steroid-ruxolitinib (5 mg/day) as first-line therapy, the ORR was 82.05%. Patients with acute GVHD grade I were also included in the phase I analysis. Thus, an expected proportion of 75% for the patients treated with steroid-ruxolitinib (5mg/day) was established. This study is planned to detect a response difference between treatment arms at a two-sided significance level α=5% with a power of 1-β=80%. The sample size was estimated using PASS software based on the primary endpoint (ORR). Allowing a withdrawal rate of 10%, 198 patients (99/group) will be required.  Continuous data are described as median with interquartile range (IQR) or mean and standard deviation (SD) according to the normality of distribution. The categorical data are described as n (%). The ORR was calculated with its 95% confidence interval (CI) and compared by the stratified Cochran–Mantel–Haenszel test. Additionally, a logistic regression model, which included aGVHD risk (high vs. intermediate), and disease status before transplantation (CR vs. no CR) as covariates, was established to explore the association between treatment and ORR on day 28. Post-hoc subgroup analysis was performed by biomarker risk, age and GVHD grade, although these were not prespecified in the protocol. The cumulative incidence of recurrent aGVHD was analysed using the Fine and Gray test in a competing risk framework. The Kaplan–Meier method was used to estimate the ORR on day 56, OS, DFS, and FFS, and the log-rank test was used to evaluate the difference between the groups. The cumulative incidence rates of NRM and relapse were estimated using a competing risk model and compared using the Fine and Gray test. A Cox proportional hazard regression model was used for multivariable regression analysis for OS and DFS. Multivariable regression analysis was performed for NRM using the Fine–Gray proportional hazard regression for competing events. The following variables were included in the univariable analysis: primary disease, cytogenetic risk, age and gender of the donor and recipient, source of graft, treatment arm, aGVHD risk, and disease status before transplantation. Variables with P<0.1 in univariate analysis or variables known to influence the outcomes were included in the multivariable analysis. Competing events were defined as follows: for GVHD, death without the event; for relapse, death without relapse; and for NRM, relapse. Any difference for which the two-sided P<0.05 was considered statistically significant. All analyses were carried out using SPSS 22.0 software (IBM Corporation, Armonk, NY, USA) or R version 4.1.2 (www.cran.r-project.org). All statistical analyses were based on the intend to treat set. \| \| | |

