# 2. STUDY OBJECTIVES AND ENDPOINTS

| Primary Objective | Primary Endpoint |
| --- | --- |
| Compare the efficacy of ruxolitinib in combination with 1mg/kg methylprednisolone versus 2 mg/kg methylprednisolone alone in terms of overall response rate (ORR) at Day 28 in subjects with acute graft-versus-host disease (acute GVHD). | ORR at Day28, defined as the proportion of participants demonstrating a complete response (CR), or partial response (PR) |
| Secondary Objective | Secondary Endpoints |
| Compare additional response and longer-term efficacy outcomes between treatment cohorts. | Durable ORR at Day56, defined as the proportion of patients in each arm whose response on day 28 lasts until day 56 after randomization. |
|  | DOR at Month 6 for responders will be calculated. The DOR is defined from the time of the onset of response to loss of response. Subjects who died or discontinued will be censored at the  death date or the previous assessment. |
|  | Response duration, defined as the time from the first response to the first recurrence/progression of acute GVHD or additional immunosuppressants for GVHD. |
|  | NRM at Month 24, defined as the time from enrollment to death due to any causes other than hematologic disease relapse. |
|  | Cumulative incidence of relapse (CIR) at Month 24, defined as the proportion of subjects whose underlying hematologic disease relapses. |
|  | Disease-free survival (DFS) at Month 24, defined as the time from enrollment to relapse of primary disease or death from any causes, whichever occurred first. |
|  | Failure-free survival (FFS) at Month 24, defined as the time from randomization to disease relapse or progression, non-relapse mortality, or the addition of new therapy for acute GVHD. |
|  | Overall survival (OS) at Month 24, defined as the time from randomization to death due to any causes. |
| Assess the incidence and severity of adverse events (AEs) and serious adverse events. | Clinical safety data (eg, AEs, infections) will be tabulated and listed. |
| Evaluate the use and discontinuation of  corticosteroids. | Average and cumulative corticosteroid dose at Days 365; proportion of subjects who discontinue corticosteroids at Days 56 and 100. |
| Evaluate the use and discontinuation of  immunosuppressive medications. | Proportion of subjects who discontinue immunosuppressive medications at Days 365. |
| Evaluate the incidence of recurrent acute GVHD. | Incidence rate of recurrent acute GVHD through Month 12. |

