### 8.3.2. Secondary Analyses

The estimated rates with two-sided 95% confidence intervals (CIs) are used for secondary endpoints (proportion of CR patients and patients who stopped treatment). The ORR on day 28 is calculated with its 95% CI. Kaplan–Meier method is used to estimate the DOR, OS, and DFS, and the log-rank test is used to evaluate the difference between the groups ^[21]^. The cumulative incidence of NRM and relapse is estimated using a competing risk model and compared using the Fine and Gray test. The Cox proportional hazard regression model is used for multivariable regression analysis for OS and DFS. The multivariable regression analysis for NRM is performed using the Fine–Gray proportional hazard regression for competing events. Potential risk factors considered in the regression analysis include primary disease, cytogenetic risk, age and gender of the donor and recipient, graft source, treatment arm, acute GVHD risk, and disease status before transplantation. The cumulative incidence of recurrent acute GVHD is analyzed using the Fine and Gray test in a competing risk framework. The threshold for statistical significance is set at 0.05, and all tests are two-sided. All analyses are carried out using SPSS 22.0 software (IBM Corporation, Armonk, NY, USA) and R version 4.1.2 (www.cran.r-project.org). The treatment-induced differences in OS and DFS will be based on the Cox proportional hazard regression model. The reported treatment difference in NRM and relapse will be based on the multivariate analysis using Fine–Gray proportional hazard regression.

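### Treatment arm is on the P<0.1 screening list for the models that supply the adjusted treatment effects on OS, DFS and NRM, and nothing forces arm or the randomisation factors into those models

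*Protocol*

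**What the plan says.** The Synopsis (Statistical Methods) lists the candidates for univariable analysis. The list starts with primary disease and cytogenetic risk and continues with "age and gender of the donor and recipient, source of graft, treatment arm, aGVHD risk, and disease status before transplantation". The selection rule follows: "Variables with P<0.1 in univariate analysis or variables known to influence the outcomes were included in the multivariable analysis". The multivariable models named there are Cox for OS and DFS, and Fine-Gray for NRM.

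Section 8.3.2 does not repeat the P<0.1 rule. It describes a set of potential risk factors to be considered, again including "graft source, treatment arm, acute GVHD risk, and disease status before transplantation". It then names the source of the treatment effects. For OS and DFS: "The treatment-induced differences in OS and DFS will be based on the Cox proportional hazard regression model". For NRM and relapse: "The reported treatment difference in NRM and relapse will be based on the multivariate analysis using Fine–Gray proportional hazard regression". The OS and DFS sentence does not say multivariable, but the only Cox model that Section 8.3.2 describes is the multivariable one.

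Two other places matter for comparison. Section 4.4 stratifies randomisation by disease status before transplantation and by acute GVHD risk. Section 8.3.1 fixes treatment and those two factors as covariates in the logistic model for the primary endpoint, with no screening.

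**The concern.** In a randomised trial, treatment is the contrast being estimated and is not a candidate prognostic factor. If arm has to pass a significance screen to enter the model that reports its effect, an adjusted estimate exists mainly when the unadjusted estimate is already large. Averaged over the trials that report one, such an estimate lies further from 1 than the truth, and its confidence interval takes no account of the selection. The model could also contain arm for one endpoint and not for another. The two randomisation factors are on the same list and could be dropped in the same way, which departs from the primary analysis for no stated reason.

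This is more than detail left to a statistical analysis plan. The Protocol states a selection rule, and that rule as worded covers treatment arm.

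**Working it through.** **The plan's own figure.** The only relevant number is the sample size. With 55% against 75%, two-sided alpha 0.05 and 80% power, the pooled-variance formula gives n = [1.960·√(2·0.65·0.35) + 0.842·√(0.55·0.45 + 0.75·0.25)]² / 0.20² = (1.322 + 0.555)² / 0.04 ≈ 88.1, so 89 per arm. Allowing 10% withdrawal, 89/0.9 = 98.9, so 99 per arm and 198 in total. This reproduces. The Protocol gives no event counts or hazard ratios for OS, DFS, NRM or relapse, so everything below rests on assumed values.

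**The screen.** With 1:1 allocation and d events, SE(log HR) ≈ 2/√d. Arm passes two-sided P<0.1 only if |log HR| > 1.645·SE.

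- Assume 60 deaths, about 30% of 198 by Month 24. SE = 2/√60 = 0.258.
- Limits: exp(±1.645·0.258) = 0.65 and 1.53. A favourable estimate must be 0.65 or lower to pass.
- True HR 0.75: log HR = −0.288. P(pass, favourable) = Φ((−0.425 + 0.288)/0.258) = Φ(−0.53) ≈ 0.30. Passing in the unfavourable direction adds about 0.003.
- Mean log HR among favourable passes = −0.288 − 0.258·φ(0.53)/Φ(−0.53) = −0.288 − 0.258·(0.347/0.298) ≈ −0.588. This is a geometric mean HR of about 0.56.
- With 50 to 80 deaths the favourable limit moves from 0.63 to 0.69, and the mean selected HR runs from 0.53 to 0.59.

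**Other assumed effects** (share of trials that keep arm, and geometric mean HR when it is kept):

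| True HR | 40 events | 60 events | 80 events |
|---|---|---|---|
| 0.80 | 18%, 0.54 | 22%, 0.58 | 26%, 0.61 |
| 0.70 | 31%, 0.49 | 40%, 0.55 | 48%, 0.58 |
| 0.50 | 71%, 0.43 | 85%, 0.47 | 93%, 0.48 |
| 1.00 | 10%, 1.00 | 10%, 1.00 | 10%, 1.00 |

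**Cox simulation.** Settings: 198 patients, 24 months, arm plus eight binary covariates, 1,500 runs per HR, and on average 41 to 54 events depending on the HR. The other covariates were screened at P<0.1 except in the fixed model, which holds arm plus two prespecified covariates.

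| True HR | Arm kept by screen | Mean HR when kept | Mean HR, arm forced in | Mean HR, fixed model |
|---|---|---|---|---|
| 0.70 | 31% | 0.504 | 0.696 | 0.693 |
| 0.50 | 68% | 0.421 | 0.498 | 0.493 |

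At true HR 1.0, rejection at the 5% level was 0.048 with arm screened, 0.049 with arm forced in and 0.051 in the fixed model. Forcing arm in removes the distortion. Screening the other covariates caused no visible bias once arm was forced in.

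**The case against.** **The rule has a second limb.** Variables known to influence the outcome enter whatever their P value, and that could cover arm and both stratification factors. If it does, no selection occurs. This stands in part: it makes the bias conditional. It does not repair the rule, because whether arm affects these outcomes is what the trial is testing, and the clause names no variables.

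**Section 8.3.2 contains no screen.** A model named as the source of the treatment difference is most naturally read as containing treatment. That is a fair reading, but the Synopsis rule sits beside it and neither text settles the matter.

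**Relapse.** The Synopsis names no multivariable model for relapse, so the P<0.1 rule reaches relapse only when the two texts are joined. This stands.

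**Unselected comparisons are planned.** For OS, DFS and FFS the Synopsis says that "the log-rank test was used to evaluate the difference between the groups", and NRM and relapse are compared by the Fine and Gray test. These do not depend on the screen. Only the adjusted estimate is exposed.

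**Stronger readings that the documents do not support.**

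- A reader might infer that the reported effects will certainly be exaggerated. That needs arm to be dropped at P≥0.1 and its effect to be reported only when kept, and the Protocol commits to neither.
- A reader might infer that false-positive findings increase. The simulation shows no inflation.
- At a true HR of 1.0, favourable selected estimates average about 0.59 with 60 deaths, but only because the favourable sign is also conditioned on. Without that condition the mean is 1.0.
- An unstratified log-rank test might be called invalid. It remains valid after stratified randomisation; stratifying it is a choice.
- NRM and DFS start at enrollment, while OS and FFS start at randomization, so DFS could exceed OS in a patient who dies without relapse. Sections 4.6 and 6.1 limit screening to one or two days, which makes this minor, although the Synopsis allows up to 28 days.

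**Conclusion.** The point holds as a defect in how the rule is fixed. Treatment arm is on the screened list, nothing forces arm or the two randomisation factors into the models named as the source of the adjusted OS, DFS and NRM effects, and the primary model does better. Relapse is affected only if the Synopsis rule is taken to apply to it.

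The harm is conditional and falls on estimation. If the adjusted effect is reported only when arm is kept, a true HR of 0.75 would appear as about 0.56 in the roughly 30% of trials that report it. This rests on 60 assumed deaths and a normal approximation for the log hazard ratio. It shrinks as events or the true effect grow: at 80 events and a true HR of 0.50, the retained mean is 0.48. The primary endpoint is not involved. The change should be made, because four secondary endpoints may take their adjusted effect from this wording.

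**What to change.** In the Synopsis and Section 8.3.2, state that treatment arm, acute GVHD risk and disease status before transplantation are always included in the Cox models (OS, DFS) and Fine-Gray models (NRM, relapse) that give the treatment effect. Remove treatment arm from the list of screened variables, and restrict the P<0.1 screen to an exploratory analysis of prognostic factors. Make the two texts agree on whether relapse has a multivariable model.

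Optional in the same edit: stratify the log-rank test by the same two factors, to match the stratified Cochran–Mantel–Haenszel test used for ORR, and use randomization as the single time origin for NRM, DFS, OS and FFS.

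The cost is a few sentences and minor programming. Both factors are already collected for randomisation, and neither the sample size nor the data collection changes.

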## 8.2. Level of Significance

The 1-sided significance level for the primary and key secondary endpoint analysis is 0.025. The 2-sided significance level for other analyses is 0.05. All CIs will be 95%.

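### Secondary comparisons are called statistically significant at two-sided 0.05 with no order, gating or supportive label, and the 'key secondary' endpoint is never named

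*Protocol*

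**What the plan says.** The protocol has one primary endpoint, Day-28 ORR, and Sections 4.5.2 and 8.1 base the sample size on it alone.

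The rule for declaring significance appears in three places:

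- Synopsis, Statistical Methods: "Any difference for which the two-sided P<0.05 was considered statistically significant".
- Section 8.3.2: "The threshold for statistical significance is set at 0.05, and all tests are two-sided".
- Section 8.2, in two sentences: "The 1-sided significance level for the primary and key secondary endpoint analysis is 0.025", followed by "The 2-sided significance level for other analyses is 0.05".

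The secondary between-arm tests are listed twice, and the lists differ.

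- The synopsis gives log-rank tests for four endpoints: "The Kaplan–Meier method was used to estimate the ORR on day 56, OS, DFS, and FFS, and the log-rank test was used to evaluate". It gives Fine and Gray tests for three more: "The cumulative incidence rates of NRM and relapse were estimated using a competing risk model and compared using the Fine and Gray test", and "The cumulative incidence of recurrent aGVHD was analysed using the Fine and Gray test in a competing risk framework".
- Section 8.3.2 has this log-rank list: "Kaplan–Meier method is used to estimate the DOR, OS, and DFS, and the log-rank test is used to evaluate the difference between the groups". It repeats the Fine and Gray tests for NRM, relapse and recurrent acute GVHD. It includes DOR but assigns no test to Day-56 ORR or FFS.

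Section 8.3.2 also says which analysis supplies the reported treatment difference: the Cox model for OS and DFS, and the multivariable Fine–Gray model for NRM and relapse. The synopsis mentions regression models but does not carry that statement.

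**The concern.** Leaving secondary endpoints unadjusted is ordinary in a phase II trial when they are presented as supportive. This protocol instead says affirmatively that each difference below 0.05 is statistically significant. Read literally, it permits a significance claim on OS, NRM, relapse or durability of response even if Day-28 ORR fails, from a set of tests with no joint error control.

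Section 8.2 looks as if it supplies a hierarchy, because it sets the primary and a key secondary endpoint apart from everything else. But neither the synopsis nor Section 2 marks any secondary endpoint as key, and no order between the two is given. A tier whose member can be picked after the results are known gives no protection. At stake is what the trial may conclude from its secondary results. The validity of the primary comparison is not in question.

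**Working it through.** **1. Sizing, as a check on what the trial was built for.** Inputs from Sections 4.5.2 and 8.1: 55% versus 75%, two-sided 5%, 80% power, 10% withdrawal; 1:1 allocation from Section 4.4. With pooled variance, no continuity correction and a mean rate of 0.65:

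n = [1.960 × √(2 × 0.65 × 0.35) + 0.842 × √(0.55 × 0.45 + 0.75 × 0.25)]² / 0.20² = 88.1, so 89 per arm.

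89 / 0.9 = 98.9, so 99 per arm and 198 in total. The stated figure reproduces, and no secondary endpoint enters it.

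**2. Counting the planned secondary tests.**

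| Endpoint | Synopsis | Section 8.3.2 |
|---|---|---|
| Day-56 ORR | log-rank | – |
| FFS | log-rank | – |
| OS | log-rank | log-rank |
| DFS | log-rank | log-rank |
| DOR | – | log-rank |
| NRM | Fine and Gray | Fine and Gray |
| Relapse | Fine and Gray | Fine and Gray |
| Recurrent acute GVHD | Fine and Gray | Fine and Gray |

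That is seven in the synopsis and six in Section 8.3.2. Eight is the union of the two lists.

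**3. What the Section 8.2 tier does.** For a result favouring ruxolitinib, one-sided 0.025 and two-sided 0.05 use the same critical value, z = 1.96. The tier is therefore no stricter than the level given to the other analyses. With no named endpoint and no order, it also does not limit which tests may be claimed.

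**4. Chance of at least one P<0.05 when no secondary endpoint has a true effect.**

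Independent tests: 1 − 0.95^k.

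- k = 7: 1 − 0.95⁷ = 30.2%
- k = 8: 1 − 0.95⁸ = 33.7%

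These endpoints overlap, so independence overstates the figure. The documents give no correlation, so a common correlation ρ is assumed and varied. Each statistic was simulated as √ρ × (shared normal) + √(1 − ρ) × (own normal), with 400,000 draws and |z| > 1.96 counted as significant:

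| ρ (assumed) | 8 tests, either direction | 8 tests, favouring ruxolitinib only | 7 tests, either direction |
|---|---|---|---|
| 0 | 33.7% | 18.3% | 30.2% |
| 0.3 | 30.0% | 15.2% | 27.2% |
| 0.5 | 25.0% | 12.5% | 23.0% |
| 0.7 | 19.2% | 9.6% | 17.7% |
| 0.8 | 15.8% | 7.9% | 14.8% |

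The bound that needs no correlation assumption is 8 × 0.05 = 40%. The protocol states no family-wise figure to compare with; its 0.05 is a per-test level.

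**The case against.** The strongest reply is that this is a phase II trial with one primary endpoint and a sample size that reproduces. Testing order and multiplicity rules for secondary endpoints commonly sit in a statistical analysis plan, which is not at hand. On that view a nominal 0.05 threshold is merely conventional. This would answer a complaint that the protocol is silent. It does not answer the point here: the protocol states a rule in both the synopsis and Section 8.3.2, and it creates a key secondary tier without a member. A later plan that added a hierarchy would have to override that text.

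Other parts of the reply stand and limit the point:

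- A reader might infer that OS, DFS, NRM and relapse each have two competing tests and that whichever is favourable may be reported. Section 8.3.2 does not support that, because it names the model that supplies the reported difference for all four.
- A reader might add chronic GVHD, response duration, and steroid and immunosuppressant use to the count. No between-arm test is specified for these, and Section 8.3.2 describes rates with confidence intervals for the proportions in CR and stopping treatment. Overlap between DOR and response duration adds no test.
- No single section plans all eight tests.
- Section 8.2 does separate the primary and a key secondary from other analyses, so it would be wrong to say that the protocol contemplates no tiers at all. The defect is that the tier is unfinished.

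**Conclusion.** The point holds as a moderate one. The protocol fixes an unadjusted rule under which any secondary difference below two-sided 0.05 is statistically significant. It neither gates this on Day-28 ORR nor labels the results supportive, and its one tiering device refers to an endpoint that it never names.

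For eight tests the chance of at least one false P<0.05 runs from about 16% (common correlation 0.8) through 25% (0.5) to 34% (independent). These figures assume that no secondary endpoint has a true effect and that all pairs share one correlation. They count results in either direction; those favouring ruxolitinib alone are roughly half as frequent.

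Two stronger readings are not supported. A reader might conclude that a false secondary claim is likely; the supportable statement is that its chance is well above 5% over the range examined, with 25% only one point in that range. A reader might also conclude that the primary result is compromised; the type I error of the single Day-28 ORR test is not affected by how the secondaries are handled.

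**What to change.** In the Synopsis and Sections 8.2 and 8.3.2, replace the general significance rule with one of the following:

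1. State that Day-28 ORR is the only confirmatory test, and that all secondary endpoints are supportive and reported as estimates with 95% CIs and nominal p-values.
2. If one confirmatory secondary is wanted, name it in Section 8.2 and test it only if Day-28 ORR succeeds. Treat all remaining secondaries as in option 1. Under option 1, delete the reference to a key secondary endpoint.

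In either case, bring the synopsis and Section 8.3.2 to a single list of tested secondary endpoints, settling whether Day-56 ORR, FFS and DOR are in it. Carry into the synopsis the Section 8.3.2 statement on which model gives the reported difference for OS, DFS, NRM and relapse.

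This needs wording changes only, with no extra patients or data. The price is that secondary results, apart from a named and gated one, can no longer be claimed as significant in their own right.
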